#### Phase 3: mixed-reality-driven virtual coach program’s system usability and predictors of intention to program participation

##### Structural equation modeling (SEM)

The popularity of structural equation modeling (SEM) as a research approach is attributed to its capacity to concurrently evaluate the validity of the measurement (55) while testing the relationship between latent variables (56). Specifically, the variance-based partial least squares (PLS-SEM) technique shall be used in the current study to maximize statistical power and deliver better convergence behavior (57, 58). UTAUT, usability, and behavioral intention variables will be processed to create a parsimonious model. An independent usability testing (59) with descriptive analysis will also be carried out.

#### Phase 4: participants’ experiences: program acceptability, barriers, and facilitators

##### Descriptive qualitative

Descriptive qualitative research is mainstream in studies exploring human phenomena in nursing and healthcare practice (60). In capturing the participants’ lived experiences with the technology, a descriptive qualitative tradition with thematic analysis (61) shall be applied. A descriptive approach, based on Husserlian principles (62), is proven powerful in clarifying poorly understood concepts of experiences (63), such as the potential acceptance, barriers, and facilitators of mixed reality health enhancing physical activity participation.

### Study setting, subject, and eligibility criteria

The study will be conducted at two senior centers in urban settings in the Philippines. The senior centers are served by a university-based medical facility located in the northern (Valenzuela City) and southern part (Quezon City) of Luzon Island in the Philippines, where the highest densities of older adults are found.

The eligible participants will be purposively selected from the regular attendees at the study sites using the inclusion criteria: (1) ambulatory, (2) can follow simple instructions, (3) normal eyes functioning without low vision (or at most with corrective lenses), and (4) willingness to participate in the program with signed informed consent. Older adults ages 60–75 regardless of the gender and who are considered fit to participate by the community physician will be targeted. A total of 128 or 64 older adults in each center, will be recruited via posters at community senior centers who will undergo additional screening or health records review by a certified gerontologist to ensure safety and proper fit. Afterward, the treatments will be assigned to each of the two senior center sites for the quasi-experimental study. Only the participants from the experimental group shall be involved in the usability evaluations and qualitative arm. The sampling plan is shown in Figure 1.

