## Abstract

**Background:**

Physical inactivity and a sedentary lifestyle among community-dwelling older adults poses a greater risk for progressive physical and cognitive decline. Mixed reality technology-driven health enhancing physical activities such as the use of virtual coaches provide an emerging and promising solution to support healthy lifestyle, but the impact has not been clearly understood.

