## Introduction

Physical inactivity, is common among older adults, affecting one-third of the global population (1, 2), and accounts for an estimated $53.8 billion global economic burden on the healthcare system (3, 4). It is also responsible for around 10% of global deaths annually (4). In the United States alone, almost 80% of older adults are considered inactive (5). Recent literature reviews reported a radical change in older adults’ lifestyles during the COVID-19 pandemic that further reduced physical activity (6, 7). In the Philippines, a survey reports that 67% percent of older adults are inactive, further exacerbated by the current pandemic (8, 9). The limitation on physical activity progresses physical deterioration and development of comorbidities and is considered a decisive risk factor for all-cause mortality (10). As an exemplar, the odds of COVID-19 death are 2.49 higher for inactive and sedentary patients (11). Therefore, there is a solid call to promote exercise programs that foster physical activity engagement and reduce sedentary lifestyle in older adults, most especially in the post-pandemic era (8, 12) since older adults are particularly susceptible of leading inactive lifestyles (13).

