## Methods

### Design

An explanatory sequential mixed-method research design will be used to understand the impact of the mixed-reality-driven virtual coach program community-dwelling Filipino older adults and compare its effects against the current exercise program (live coaching and video-based) on the participants’ health. The current study advances four (4) research phases that will make use of distinct research approaches. Phases 1–3 shall adopt a post-positivist approach (46) through discreet choice experiment (conjoint analysis), quasi experiment, and structural equation modeling. Phase 4 follows a qualitative-constructivist paradigm (47) using descriptive qualitative research.

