### Comparing the effects of the mixed reality technology-driven health enhancing physical activities with the usual health enhancing physical activities (live coach and video-based) on participants’ physical, cognitive status, and quality of life measures

#### Repeated measures analysis of variance (RM-ANOVA)

Repeated Measures Analysis of Variance (RM-ANOVA) will be used to investigate the effects of the type of intervention on health variables across three assessment points using SPSS version 22. Mauchly’s Test will be utilized to verify the sphericity assumption with degrees of freedom correction using the Greenhouse–Geisser method. Effect sizes will also be reported.

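### Prior exercise is neither restricted nor evidently measured among regular center attendees, and with one treatment per center it is confounded with the comparison, in an uncertain direction

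*Protocol article*

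**What the plan says.** The rationale concerns inactive people. The abstract's Background opens with "Physical inactivity and a sedentary lifestyle among community-dwelling older adults poses a greater risk for progressive physical and cognitive decline", and the Introduction, which cites 67% inactivity among older adults in the Philippines, adds that "there is a solid call to promote exercise programs that foster physical activity engagement and reduce sedentary lifestyle in older adults".

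The section on study setting, subject and eligibility then fixes the source pool: "The eligible participants will be purposively selected from the regular attendees at the study sites using the inclusion criteria". The listed criteria are "1) ambulatory, (2) can follow simple instructions, (3) normal eyes functioning without low vision (or at most with corrective lenses") and willingness with signed consent. Age and fitness are added: "Older adults ages 60–75 regardless of the gender and who are considered fit to participate by the community physician will be targeted". There is also "additional screening or health records review by a certified gerontologist to ensure safety and proper fit". None of these mentions activity level, sedentary status or earlier use of an exercise program. The same section assigns one treatment to each center.

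The comparator is described twice as something already in place. The Design section plans to "compare its effects against the current exercise program (live coaching and video-based"), and the heading over the RM-ANOVA plan sets mixed reality against it "with the usual health enhancing physical activities (live coach and video-based").

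Table 2 (Outcomes) covers the 6-minute walk, MoCA, SF-8, demographics, technology literacy, depression, anxiety, sleep and a self-care inventory classed as health behavior. No entry is labelled habitual physical activity or prior program participation.

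**The concern.** Read together, these statements admit a regular attendee who already takes part in the live or video program. At the control center such a person continues what they were doing, so their baseline is not a pre-exposure value. At the experimental center the same kind of person changes format. Others at either center start from no exercise. The comparison then mixes continuing versus switching with starting versus starting, in unknown proportions that may differ between centers.

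Three features make this matter more than it usually would:

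- Treatment is assigned by center, so a difference between the centers in prior exercise cannot be separated from the treatment effect by design.
- Exposure is short: two weeks at two sessions and two weeks at three, that is 2×2 + 2×3 = 10 sessions. People who are already trained may have little further to gain.
- The Objectives hypothesize comparable results and the article states no margin. A small observed difference could be taken as support for the hypothesis when it partly reflects who was enrolled.

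**Working it through.** **Inputs from the article.** 64 per center, power 0.80, alpha 0.05, effect size given only as medium to high (Sample size); 67% inactive (Introduction), hence 100 − 67 = 33% active in the general older population; one treatment per center (eligibility section).

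**Assumptions, not in the article.** Standardized effect 0.5 SD (a conventional medium value); two-sided testing; share of attendees already exercising *p* = 20–50%, which brackets the 33%; already-exercising people who are at a plateau gain nothing in the month. All figures treat the comparison as a two-sample test on a standardized scale.

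**1. The plan's own figure.** The normal approximation gives n = 2(1.960 + 0.842)² / 0.5² = 62.8, so 63 per arm. The t-test gives 63.8, so 64 per arm and 128 in total. Power at 64 per arm is 0.801. The stated 128 is reproduced at 0.5 SD, so that value is a reasonable yardstick below.

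**2. Plateau in controls only, programs truly equal.** If controls who are already in the program gain nothing while everyone else gains *g*, the spurious contrast is *p* × *g*, in favor of mixed reality.

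| *p* | *g* | False contrast | Chance of significance at 64 per arm |
|---|---|---|---|
| 0.25 | 0.5 SD | 0.125 SD | 0.11 |
| 0.50 | 0.5 SD | 0.25 SD | 0.29 |
| 0.25 | 0.3 SD | 0.075 SD | 0.07 |
| 0.50 | 0.3 SD | 0.15 SD | 0.13 |

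**3. Plateau in both arms, programs truly different by 0.5 SD.** The contrast shrinks to 0.5(1 − *p*).

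- *p* = 0.25: 0.375 SD, power 0.56; 113 per arm would be needed for 80%.
- *p* = 0.50: 0.25 SD, power 0.29; 253 per arm would be needed.

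Here the error runs toward apparent comparability.

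**4. Plateau in both arms, equal programs, unequal shares.** With an assumed 20% already exercising at one center and 50% at the other, mean gains are 0.5 × 0.80 = 0.40 SD and 0.5 × 0.50 = 0.25 SD. Identical programs differ by 0.15 SD. The sign depends on which center has more exercisers.

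**5. Cost of making non-exercisers the main contrast.** If 20%, 33% or 50% are already active, 64 × 0.80 = 51, 64 × 0.67 = 43 or 64 × 0.50 = 32 per arm remain. Power at 0.5 SD falls from 0.80 to 0.71, 0.63 or 0.50 unless recruitment is enlarged.

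Steps 2 to 4 start from the same gap and point in different directions. Without a record of prior exposure, there would be no way to tell which applied.

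**The case against.** The strongest reply is that the article never says participants must be inactive or new to exercise. Its stated target is community-dwelling older adults, with inactivity as background, and a comparison with a usual program can properly include that program's current users. A regular attendee of a senior center is not necessarily a regular of an exercise class. Live coaching with video is presented as one of two treatments assigned to a site after recruitment, so the words current and usual may mean only the conventional mode of delivery. All of this stands. A reader might infer that the rationale and comparator require non-exercisers, or that controls are already on treatment at baseline; the article supports neither.

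A reader might also infer that controls continuing their program dilutes the change in both arms and so pushes the result toward comparability. That does not follow. Continuation flattens the control arm alone and favors mixed reality. Dilution in both arms needs the further assumption that earlier exercise limits gains in the new format too.

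It is also fair that this is a condensed article, that the items of the health-behavior inventory and the content of the fitness screening are not shown, and that baseline assessment is planned. It would therefore be too strong to say that prior exposure could never be recovered. But baseline walking capacity is not a record of program use, and a self-care inventory is not evidently one. The article does state its criteria, source pool, comparator and instrument list, and the weakness lies in how these combine.

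**Conclusion.** The point holds as a gap in control of confounding. Prior exercise is a plausible strong determinant of one-month change; it is neither restricted by the stated criteria nor evidently measured, and treatment is assigned by center. The direction of the resulting bias is uncertain: toward mixed reality if only controls are at a plateau (0.125–0.25 SD for 25–50% of controls, with a true gain of 0.5 SD), and toward comparability if room to improve is limited in both arms. Neither a comparable nor a different result could then be attributed to the technology with confidence.

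The size is illustrative. The 67% inactivity figure describes older adults in the Philippines, not center attendees. The share already exercising, the 0.5 SD gain and the zero gain in exercisers are all assumed. The case for acting rests on the low cost of the measurement and on the need to have it in place before enrolment.

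**What to change.** At the existing screening, and identically at both centers, record (a) current or recent participation in the center's live or video program or in another structured exercise program, within a look-back period the sponsor fixes in advance, and (b) weekly physical activity. Then:

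- report both by center at baseline;
- adjust the between-program comparison of change for them, entering each with its interaction with assessment time so that it can act on change and not only on level;
- show the comparison among participants not currently exercising as a sensitivity analysis.

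The last item is needed because a covariate with one common effect corrects for different shares at the two centers, but not for a plateau that occurs in the control arm only. It should not become the main contrast, given the loss of power in step 5. None of this removes other differences between the two centers.

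The cost is one or two screening questions and one or two covariates. Excluding current exercisers, or capping them equally at each center, is an option for the sponsor: it gives a cleaner contrast but gives up generalizability and recruitment speed.

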**Methods and analysis:**

An observational explanatory sequential mixed-method research design was conceptualized to examine the potential impact of a user-preferred mixed reality technology-driven health enhancing physical activity program directed toward purposively selected community-dwelling older adults in two senior centers in the Philippines. Quantitative components of the study will be done through a discreet choice experiment and a quasi-experimental study. A total of 128, or 64 older adults in each center, will be recruited via posters at community senior centers who will undergo additional screening or health records review by a certified gerontologist to ensure safety and proper fit. Treatments (live coaching with video-based exercise and mixed reality technology-driven exercise) will be assigned to each of the two senior center sites for the quasi-experiment. The participants from the experimental group shall be involved in the discreet choice experiment, modeling, and usability evaluations. Finally, a qualitative sample of participants (*n* = 6) as key informants shall be obtained from the experimental group using purposive selection.

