#### Phase 2: impact of mixed-reality-driven virtual coach program on participants’ physical, cognitive status, and QoL

##### Quasi experiment

Quasi experimental research will be employed to estimate the effect and examine the causal relationship between the HT-HEPA intervention and the study respondents’ physical, cognitive status, and QoL. Quasi experiments are appropriate for practical situations and ethical compliance for studies involving vulnerable participants such as older adults (53), and allow scholars to conduct rigorous studies under certain limitations and non-control conditions (54).

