### Sample size

To identify the acceptable sample size, the difference in repeated measures between two independent groups using MANOVA with a power set at 0.80 with medium to high effect size at 0.05 alpha level was computed using R software. The estimated sample size is 128 or 64 participants per senior center group.

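### With one senior centre per programme, Phase 2 cannot support a causal claim, and the stated power and alpha hold only if there is no centre effect on change

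*Protocol article*

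**What the plan says.** The Protocol article fixes the allocation in three places.

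- Study setting, subject, and eligibility criteria: "The study will be conducted at two senior centers in urban settings in the Philippines". They lie in different cities. On recruitment: "The eligible participants will be purposively selected from the regular attendees at the study sites". On allocation: "Afterward, the treatments will be assigned to each of the two senior center sites for the quasi-experimental study".
- Abstract, Methods and analysis: "Treatments (live coaching with video-based exercise and mixed reality technology-driven exercise) will be assigned to each of the two senior center sites for the quasi-experiment".
- Sample size: "The estimated sample size is 128 or 64 participants per senior center group". Group and centre are treated as the same thing.

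On what is to be concluded, the Phase 2 section (Quasi experiment) says the study will "estimate the effect and examine the causal relationship between the HT-HEPA intervention" and the participants' physical status, cognitive status and quality of life. Quantitative aim 2 under Objectives also speaks of a causal relationship.

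On power, the Sample size section bases its figure on "the difference in repeated measures between two independent groups using MANOVA", with "power set at 0.80 with medium to high effect size at 0.05 alpha level". The analysis section plans a repeated measures ANOVA by type of intervention over three assessment points. None of these sections mentions a centre effect or correlation within centres.

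**The concern.** Assignment is by centre, and there is one centre per programme. Programme and centre are then a single variable in the data. If attendees at one centre improve more for a local reason, the analysis attributes that improvement to the programme received there.

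The error can go either way. A centre effect can look like a programme difference, or it can cancel a real one. Cancellation matters here because the protocol hypothesises comparable results under the two programmes, so a masked difference would read as confirmation.

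This is not a detail that a statistical analysis plan could settle. A site term would be perfectly collinear with treatment. The problem lies in the design, the claim and the basis for the power figure, all of which the protocol itself states.

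**Working it through.** **1. The plan's own figure.** The effect size is given only in words and sidedness is not stated. Assume a standardised difference d = 0.5, two-sided alpha 0.05, 1:1 allocation and independent people. The exact noncentral t calculation gives 64 per group, 128 in total, with power 0.801 (63 per group gives 0.795). So 128 is reproduced, as a comparison of independent individuals.

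**2. What the contrast estimates.** Let τ be the programme effect on change, and γ₁ and γ₂ the centre-specific changes that would occur under a common programme. The expected difference in change between the groups is

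τ + (γ₁ − γ₂).

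Stable level differences cancel on subtracting baseline; γ₁ − γ₂ does not. A centre-level test has 2 centres − 2 programmes = 0 degrees of freedom, so the data cannot show whether γ₁ − γ₂ is zero.

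**3. Illustrative size.** The protocol gives no centre-level ICC; the ICCs in its Table 2 are instrument reliabilities. Assume that centre effects on change account for a share ICC of the variance, with n = 64 per centre and d = 0.5.

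- Variance of the difference, in SD² units: 2[ICC + (1 − ICC)/n] = (2/n)(1 + 63·ICC).
- Design effect: DE = 1 + 63·ICC.
- Type I error of the planned test, which ignores centre: 2[1 − Φ(1.96/√DE)].
- Power of a test that allows for the centre variance, with the ICC treated as known: Φ(0.5·√(64/2)/√DE − 1.96) = Φ(2.828/√DE − 1.96).

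| Assumed ICC of change | DE | Type I error of planned test | Power, ICC known |
|---|---|---|---|
| 0 | 1.00 | 0.050 | 0.807 |
| 0.01 | 1.63 | 0.125 | 0.60 |
| 0.02 | 2.26 | 0.19 | 0.47 |
| 0.05 | 4.15 | 0.34 | 0.28 |

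The 0.807 in the first row is the normal approximation to the 0.801 in step 1.

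**4. More participants would not cure it.** Power of 0.80 needs 2[ICC + (1 − ICC)/n] ≤ (0.5/(1.960 + 0.842))² = 0.0319. As n grows, the left side falls only to 2·ICC. Under these assumptions, no number of participants at two centres reaches 0.80 once the ICC is about 0.016 or more.

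**The case against.** Several points on the other side have force.

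- **Baseline is measured.** A reader might infer that every difference between the centres is indistinguishable from the treatment effect. The documents do not support that. There is a baseline assessment and a repeated measures analysis, so in a group-by-time contrast stable differences in case mix or fitness cancel. Only centre-specific change over a programme of about one month remains. The type of coach is largely the treatment contrast itself, and nothing says that season or assessors differ between centres. Participants are to be supervised under a standard protocol.
- **The design is declared non-randomised.** The abstract calls the study observational and quasi-experimental, and Phase 2 gives practical and ethical reasons and acknowledges limitations in general terms. Non-random assignment is not hidden. However, the one-centre-per-programme problem is not named, and the causal wording stands in the same section.
- **The sample size is not miscalculated.** A reader might infer that 128 is wrong. It is reproduced; what is missing is the condition under which its power applies.
- **The losses are not established.** Both the ICCs and the 0.5 SD effect are assumptions. The powers also treat the ICC as known, which two centres cannot provide, so they are optimistic for any given ICC.
- **Type I error is not the main risk to a hypothesis of comparability.** This is fair. For that conclusion, masking of a real difference matters more.

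None of this separates programme from centre-specific change.

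**Conclusion.** The point holds in a limited form. The allocation in the protocol makes programme and centre the same variable, so the causal wording in Phase 2 and aim 2 is unsupported. The 0.80 power and 0.05 alpha are correct only if there is no centre effect on change, a condition that the study cannot test and the protocol does not state.

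The size of the departure is illustrative: type I error of about 0.125 to 0.34 and power of about 0.60 to 0.28 for assumed ICCs of change from 0.01 to 0.05, with d = 0.5, a two-sided test and 64 per centre. If the ICC of change were zero, the stated figures would stand.

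A reader might go further and conclude that the trial has to be redesigned. The documents do not require that. A non-randomised comparison of two centres can be run and reported, provided that it is described as one.

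**What to change.** Three changes are needed.

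1. **Claim.** In Quantitative aim 2 and in Phase 2 (Quasi experiment), remove the causal wording. There, in the Design section, and in the heading and text of the repeated measures ANOVA section, replace the language of programme effects with, for example: *a comparison of change between two senior centres that received different programmes; centre-specific change cannot be separated from programme effect.*
2. **Power.** In the Sample size section, add that the 0.80 power and 0.05 alpha are conditional on there being no centre effect on change, and that two centres cannot verify this.
3. **Sensitivity table.** Beside each unadjusted interval, report intervals widened by √(1 + 63·ICC) for assumed ICCs of 0.01, 0.02 and 0.05, which are factors of 1.28, 1.50 and 2.04. For a standardised difference, the unadjusted 95% half-width of 1.979·√(2/64) = 0.35 SD becomes 0.45, 0.53 and 0.71 SD. Label the table illustrative. These intervals are valid only if the assumed ICC is right, and they do not remove the confounding.

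The cost is a weaker claim and a small extra table; no participants, visits or measurements are added.

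An optional redesign is to offer both programmes within each centre and fit centre as a fixed effect. This would separate programme from centre with the same 128 people. It needs equipment and coaching at both centres, and it brings a risk of contamination. If the programmes run in separate session slots, programme is aliased with slot and people in the same sessions may be correlated. It is a choice for the sponsor, not a required correction.
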